## Summary

Depression causes work disability and impairs the quality of life (World Health Organization, 2023). There is substantial evidence of the association between nutrition and depression, but there is a lack of research on intervention studies on depressive symptoms among high-risk groups. Based on epidemiological evidence, a healthy diet can potentially reduce depressive symptoms (Gianfredi et al., 2023). Lifestyle interventions have shown benefits for working capacity and productivity (Grimani et al., 2019). As a risk group for depressive symptoms and related work disability, mental health nurses are a crucial target group for nutrition trials (Brandford and Reed, 2016).

The Mind Nutrition randomized controlled trial is the first study investigating the effectiveness of nutrition counselling on depressive symptoms, depressive symptoms–related sick leave days, work ability and the quality of life among mental health professionals. The strengths of this intervention study include the randomized, controlled study design and the combination of individual and group-based nutrition counselling grounded on theoretical frameworks that support long-term lifestyle changes (Miller, 1996; Nelson, 2017; Teixeira et al., 2015). Both individual and group counselling have been effective in dietary interventions for reducing depression (Bayes et al., 2022; Jacka et al., 2017; Parletta et al., 2019).

One limitation is the lack of blinding of the participants and study staff in this type of intervention. However, this is unlikely to cause bias for the investigators, as the data come from questionnaires completed by the participants and because the intervention provider will not analyse the data. The second limitation concerns the issues related to the questionnaires, such as temporal variability and treatment expectations that can influence the responses. However, we will use validated questionnaires to minimize these issues. The third potential limitation is that subjects randomized to the control group might withdraw from the study. We try to reduce the risk by offering them one nutrition counselling session, feedback on their food records and a personal nutrition plan after the intervention. The fourth possible limitation is that the participants in both groups may modify their eating habits because they are aware of being observed, the phenomenon known as the Hawthorne effect (Sedgwick and Greenwood, 2015). Moreover, participants in the intervention and control groups may have different treatment expectancies that can influence their behavioural and self-reported outcomes.

This study will provide novel evidence of the effectiveness of nutrition counselling on depressive symptoms among mental health and substance abuse professionals. Based on the acquired knowledge, prevention programmes can be implemented for the targeted population to sustain their mental health, quality of life and work ability.

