#### Recruitment

We will organize an informational online meeting for targeted participants in which we will explain the study procedure (Figure 1). Interested participants can register for the second informational meeting, consisting of a detailed description of the study, the inclusion and exclusion criteria and the instructions for filling in the questionnaires and food records. The principal researcher will evaluate the eligibility of the interested participants who can give informed consent at the end of the second meeting. Subsequently, we will schedule individual appointments with a research nurse and ask the participants to fill in the questionnaires before the appointments. The research nurse will measure blood pressure and weight, check the questionnaires and confirm whether the subject is eligible to participate. If the questionnaires reveal something that falls under the exclusion criteria, the research nurse can consult with the responsible physician. Exclusion of the participant is possible at this point.

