### Measurements

#### Background measurements

Background information will be collected before the randomization, utilizing the electronic survey data, and the weight and blood pressure measured at the research nurse appointments. The electronic survey will have questions about family relations, education, basic employment information and lifestyle habits, including the AUDIT-C (Saunders et al., 1993). The research nurse appointments will be organized at the university. The nurse will check the electronic questionnaire, blood pressure and weight during these appointments. We will calculate body mass index based on the measured weight and participants’ self-reported height. Although the primary focus of our intervention is not on body weight loss, we will measure it to consider the possible effect that weight loss could have on depression scores (Patsalos et al., 2021).

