#### Primary and secondary outcomes

Table 1 presents the primary and secondary outcomes. The outcomes will be assessed utilizing the electronic survey at baseline and after 6 months.

**Table 1. table1-02601060251332358:** Primary and secondary outcomes.

Primary outcome variables	Measurement
Depressive symptoms	CES-D (Radloff, 1977)
Work ability	Current work ability compared with the lifetime best (Tuomi et al., 2007) Three-level work ability indicator (Gould et al., 2015)
Secondary outcome variables	Measurement
Sick leave days related to depressive symptoms	Structured question about sick leave days during the past 6 months
Quality of life	WHO8-EUROHIS (WHO, Power, 2003)
Dietary habits	Food Frequency Questionnaire (Männistö et al., 1996) Healthy Diet Index (HDI; Lindström et al., 2021) Three-day food records Three Factor Eating Questionnaire – 18 (TFEQ-18; Karlsson et al., 2000)
Intervention adherence	Goal Attainment Scaling (GAS; Kiresuk and Sherman, 1968) Level of participation
Intervention acceptability	The Theoretical Framework for Acceptability (TFA; Sekhon et al., 2022)

CES-D: Center for Epidemiological Studies – Depression; TFEQ-18: Three Factor Eating Questionnaire – 18; WHO: World Health Organization.

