##### Acceptability

We will measure the level of intervention acceptability with Sekhon's theoretical framework of acceptability (Sekhon et al., 2022) that delineates acceptability across seven dimensions – affective attitude, burden, ethicality, intervention coherence, opportunity costs, perceived effectiveness and self-efficacy – each accompanied by pertinent questions. We will use the adapted and translated version of the generic questionnaire to measure acceptability and obtain feedback. Table 2 summarizes all the measurements and time points.

**Table 2. table2-02601060251332358:** All measurements and time points.

	Baseline measurements		Final measurements at 6 months		Others
	Electronic survey	Research nurse appointment	Electronic survey	Research nurse appointment	
Background information	X	X			
Health information	X	X	X	X	
Blood pressure		X		X	
Weight		X		X	
Depressive symptoms (CES-D)	X		X		
Work ability (two indicators)	X		X		
Sick leave days	X		X		
Quality of life (WHO8-EUROHIS)	X		X		
Diet quality (Food Frequency Questionnaire)		X		X	
Nutrient intake (3-day food records): Healthy Diet Index (HDI)	X^1^		X^1^		
Eating behaviour (TFEQ-18)	X		X		
Goal attainment (GAS): During the intervention					X
Intervention adherence (during the intervention)					X
Acceptability (TFA)			X		

CES-D: Center for Epidemiological Studies – Depression; GAS: Goal Attainment Scaling; TFA: Theoretical Framework of Acceptability; TFEQ-18: Three Factor Eating Questionnaire – 18; WHO8-EUROHIS: World Health Organization EUROHIS.

^1^
Eat@Work mobile app.

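### The low-bias argument for unblinded staff rests on self-completed data, yet Table 2 puts the 6-month FFQ, weight and blood pressure at a research nurse visit that could be masked cheaply

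*Protocol article*

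**What the plan says.** Four places in the protocol article bear on this.

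- **Summary, limitations paragraph.** "One limitation is the lack of blinding of the participants and study staff in this type of intervention". No staff role is exempted. The article then considers bias on the investigators' side unlikely, "as the data come from questionnaires completed by the participants and because the intervention provider will not analyse the data".
- **Table 2 (under Acceptability).** Under the column group "Final measurements at 6 months" there is a research nurse appointment as well as the electronic survey. The appointment is marked for health information, blood pressure, weight and the row beginning "Diet quality (Food Frequency Questionnaire". The FFQ carries no mark under the electronic survey at either time point.
- **Primary and secondary outcomes.** "The outcomes will be assessed utilizing the electronic survey at baseline and after 6 months". Table 1, in the same section, lists the FFQ and the Healthy Diet Index under dietary habits, a secondary outcome.
- **Recruitment and Background measurements.** Recruitment says: "The research nurse will measure blood pressure and weight, check the questionnaires and confirm whether the subject is eligible to participate". Background measurements says: "The nurse will check the electronic questionnaire, blood pressure and weight during these appointments". The latter section opens by fixing its timing: "Background information will be collected before the randomization".

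**The concern.** In a counselling trial the participants and the counsellor cannot be blinded. A person who only takes follow-up measurements usually can be. The limitations paragraph does not separate the two. It treats all staff alike and relies on self-completion to argue that little harm follows.

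That reason does not cover everything Table 2 assigns to the nurse. Weight and blood pressure are staff measurements, not questionnaire answers. The FFQ is a questionnaire, but the table places it at the visit, and the article does not say whether the participant fills it in alone or with help. If a nurse who knows the group helps with it, clarification could differ between arms on the very behaviour the intervention is meant to change. Weight matters indirectly, because Background measurements says it is collected to weigh the possible effect of weight loss on depression scores.

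**Working it through.** No arithmetic decides this point; the check is a side-by-side reading.

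1. **Is there a nurse visit after randomization?** Yes. Table 2 has a research nurse column at 6 months with four marks: health information, blood pressure, weight and FFQ.

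2. **Does the self-completion argument cover what happens there?** Not for weight and blood pressure, which the nurse takes. For the FFQ it depends on the mode, and the article gives two answers: the outcomes text says electronic survey, while Table 2 says nurse appointment only, at both time points. These must be reconciled.

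3. **Does any described task require the nurse to know the allocation?** None is stated.
   - Randomization: someone outside the study performs it.
   - Individual counselling: the research nutritionist gives it.
   - Statistical analyses: a statistician outside the study does them.
   - Group counselling: the section does not name who leads the sessions. I assume that it is not the nurse.

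4. **Which outcomes could be touched?**
   - CES-D, both work ability items, sick leave, quality of life and TFEQ-18 are marked under the electronic survey only.
   - The FFQ is marked under the nurse only. The dietary-habits section derives the Healthy Diet Index from the FFQ, so the index would follow it. Table 2 instead writes the index into the food-record row, which is a further wording mismatch.
   - Weight and blood pressure are not in Table 1.

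5. **Is a questionnaire check by the nurse at 6 months stated?** No. Both descriptions of the check belong to the appointment before randomization: one serves eligibility, the other background data. At that time there is no group to know.

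6. **Size.** The document gives nothing from which a bias could be calculated. At the stated 25% dropout, 125 × (1 − 0.25) = 93.75, so about 94 participants would reach the 6-month visit. That is the number of visits concerned, not a measure of bias. Masking the nurse does not alter the sample size of 125.

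**The case against.** The strongest reply is that the mechanism is mostly inferred. A reader might infer that the nurse goes through questionnaire answers face to face at 6 months while knowing the group. The article does not say so: the check is described only for the appointment before randomization. The plural in Background measurements, and the 6-month mark for health information under both survey and nurse, leave a later check possible but do not establish it. This part of the objection stands in full.

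A reader might also infer that the nurse administers the FFQ. That rests on a column mark. The instrument is described as fixed-format, with set portions and nine frequency options, and no interviewer is mentioned. The outcomes sentence is itself a loose summary, since food records come through an app and goal attainment is scored in the counselling sessions. So the conflict may be only one of wording. It still has to be resolved, because the mode decides whether the nurse matters for a listed outcome.

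Third, the article never names the nurse as unmasked; it speaks of study staff in general. Access to the allocation list and visit instructions may stand in a full protocol that is not shown. That is fair, and their absence is not the complaint. What the article does state is an unqualified lack of staff blinding and a reason for discounting it that does not match its own schedule.

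Finally, the participants know their group and report the primary outcomes themselves. The article already acknowledges treatment expectations and the Hawthorne effect. Masking the nurse removes neither. This limits the value of the change but does not make it pointless for the FFQ and weight.

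**Conclusion.** The point holds in a narrow form and is minor: a cheap improvement rather than a defect that threatens the trial. The limitations paragraph discounts unblinded staff for a reason that does not cover nurse-measured weight and blood pressure, nor the FFQ if the nurse takes part in it. The outcomes text and Table 2 also disagree on how the FFQ is collected.

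The reach is at most one secondary outcome (FFQ and Healthy Diet Index) and two measurements outside Table 1. It would be tempting to conclude that the primary results are exposed to assessor bias. The document does not support that, because CES-D and both work ability items are marked as electronic survey only.

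The conclusion rests on three assumptions: that study staff includes the research nurse, that the nurse has no unstated part in counselling, and that the Table 2 marks show where each measure is actually collected. How the nutritionist handles the food records is a separate question.

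**What to change.** 1. Keep the research nurse unaware of allocation at the 6-month appointment: no access to the allocation list, no role in counselling or in booking sessions, and participants asked beforehand not to mention their group.
2. Have the electronic survey, and the FFQ if it is self-completed, submitted before the appointment. If the nurse then looks at the survey at all, limit this to completeness and hide the acceptability section, which would presumably reveal who was counselled.
3. State the FFQ mode once, and make the section on primary and secondary outcomes and Table 2 agree. At the same time, align the table's placement of the Healthy Diet Index with the dietary-habits section.
4. Reword the limitations paragraph so that the claim of little bias covers only data that no unmasked person handles, and say which staff are masked.

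The cost is an instruction to existing staff, a change in survey timing and a few edited sentences, with no extra assessor. The drawback is that some participants will disclose their group, so masking will be partial. Recording whether the nurse learned the group at each visit would show how far it held.
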